# Acupressure therapy and Liu Zi Jue Qigong for pulmonary function and quality of life in patients with severe novel coronavirus pneumonia (COVID-19): a study protocol for a randomized controlled trial

**DOI:** 10.1186/s13063-020-04693-5

**Published:** 2020-08-27

**Keywords:** COVID-19, Acupressure therapy, Liu Zi Jue Qigong, Traditional Chinese medicine rehabilitation, Randomized controlled trial, Study protocol

## Abstract

**Background:**

In December 2019, pneumonia associated with the 2019 novel coronavirus (COVID-19) emerged in Wuhan, China. The number of cases has increased rapidly. Patients with severe disease have a poor prognosis, and there are no effective therapies for COVID-19. Only rapid advice guidelines for symptomatic supportive care have been used. A traditional Chinese medicine rehabilitation (TCMR) program consisting of acupressure therapy and Liu Zi Jue Qigong can be used as a complementary therapy for COVID-19. Hence, we designed a randomized trial to evaluate the efficacy and advantages of TCMR for treating patients with severe COVID-19.

**Methods/design:**

This is a parallel-design, two-arm, analyst assessor-blinded, randomized controlled trial. A total of 128 patients with COVID-19 aged from 20 to 80 years will be recruited and assigned randomly into a guideline therapy group and a guideline therapy plus TCMR group at a 1:1 ratio. Patients in both groups will receive guideline therapy. The patients in the intervention group will perform acupressure therapy and Liu Zi Jue Qigong exercises in addition to conventional treatments twice a day and will be persistent from admission to discharge. The primary outcome will be measured with the Modified Medical Research Council Dyspnea Scale, and the secondary outcomes will include the Activities of Daily Living Barthel Index Scale, Patient Health Questionnaire-9 Scale, and the Respiratory Symptoms Scale. The assessments of the clinical scales will be performed at three points (before treatment, the 7th day during hospitalization, and the discharge day). Adverse events will be noted and recorded for the safety evaluation.

**Discussion:**

This trial will provide high-quality evidence of the value of TCMR, which consists of acupressure therapy and Liu Zi Jue Qigong exercises, for treating patients with severe COVID-19.

**Trial registration:**

Chinese Clinical Trial Registry ChiCTR2000029994. Registered on 18 February 2020

## Background

Since December 2019, some patients with pneumonitis infected by a new type of coronavirus called COVID-19 were successively found in Wuhan, which raised intense attention worldwide [1]. COVID-19 is a novel type of coronavirus belonging to the family beta-coronavirus, and its gene sequence is significantly different from previous viruses [2]. COVID-19 is mainly transmitted through respiratory droplets and contact and has high infectiousness. Though the authorities gave the highest priority to prompt prevention and treatment of COVID-19, cases of human-to-human transmission are gradually expanding domestically and abroad. As of 27 May 2020, more than 5,406,282 people have been infected, and more than 343,562 deaths have occurred globally [3]. Patients often develop dyspnea or hypoxemia 1 week after the onset of symptoms, and in severe cases, they progress rapidly to acute respiratory distress syndrome, septic shock, etc. [4]. An early study proved that due to a shortage of medical resources, the mortality rate of patients with severe pneumonia is as high as 61.5% [5]. Eventually, the National Diagnostic and Treatment Protocol for Novel Coronavirus Pneumonia (the 7th trial version) was developed to reduce mortality and reinfection [6]. However, more options should be explored to cope with this event [6, 7]. Acupressure is a low-risk physical therapy that is different from acupuncture and is a part of traditional Chinese medicine (TCM). Previous research has shown that acupressure can improve patients’ symptoms of dyspnea in lung diseases and their quality of life [8, 9]. Acupressure is a noninvasive treatment accepted by patients; this treatment is characterized by pressing on acupoints with the hands to achieve clinical efficacy. In addition, Liu Zi Jue Qigong exercises have also been widely used in lung rehabilitation training; these exercises not only relieve symptoms of breathlessness but also have benefits on mental illness [10–12]. Liu Zi Jue Qigong is applicable for the patients with COVID-19 who widely suffer panic and anxiety due to the mortality and infectivity of the disease [13]. These exercises adopt a combination of abdominal breathing and lip breathing to produce six different sounds (xu, he, hu, si, chui, and xi) accompanied by low-intensity body movements [12]. This breathing pattern can change the rapid shallow breathing pattern of lung dysfunction, extend the opening time of the trachea, and maintain the airway pressure of the patient within a physiological range, thereby improving gas exchange [14, 15]. Regarding COVID-19 patients, dyspnea is the most obvious clinical symptom. Furthermore, sudden illness and fear of disease are psychological disorders that each patient will have. Previous studies have shown that acupressure and Liu Zi Jue exercises can improve the respiratory symptoms of patients with lung disease as well as improve their quality of life and mental health. Therefore, effectively combining the two interventions into a rehabilitation method can potentially be used in the clinical rehabilitation of COVID-19 patients. Now, we will combine the acupressure therapy with Qigong exercises as a clinical traditional Chinese medicine rehabilitation (TCMR) method for patients with severe pneumonia. Therefore, we hypothesize that official conventional therapy plus TCMR will have better clinical efficacy than single conventional therapy for clinical symptoms, mental health, and quality of life.

## Methods/design

### Study design

This will be a single-center, parallel-arms, superiority randomized controlled trial (RCT). The protocol was registered with the China Clinical Trial Registry (item number: ChiCTR2000029994), and the trial protocol was approved by the Ethics Committee of Huangshi Hospital of Traditional Chinese Medicine (item number: HSZYYJ-2020-003-01). A total of 128 patients will be recruited from the Huangshi Hospital of Traditional Chinese Medicine in Hubei province. Written informed consent will be provided by all patients at the time of recruitment. Patients with severe pneumonia symptoms will be recruited and will have equal chances of being allocated randomly to guideline therapy or guideline therapy plus TCMR. Due to the limitations of the intervention methods, only the outcome assessors and statisticians will be blinded. The assessor will perform evaluations and analysis of the outcomes at three points (before treatment, the 7th day during hospitalization, and the discharge day). Data management and statistics will be conducted at the Rehabilitation Medical College of Shanghai University of Traditional Chinese Medicine (SUTCM). The flow chart in Fig. 1 illustrates the study design, and Fig. 2 shows the study schedule. Additional file 1 shows the Standard Protocol Items: Recommendations for Interventional Trials (SPIRIT) checklist.

**Fig. 1 Fig1:**
[figure not shown]
Flow chart of the trial

**Fig. 2 Fig2:**
[figure not shown]
Study schedule showing the time points for enrollment and assessment. ADL, activities of daily living; CRF, case report form; CT, computed tomographic; mMRC, modified Medical Research Council; PHQ-9, Patient Health Questionnaire-9; RS, respiratory symptoms; TCMR, traditional Chinese medicine rehabilitation

### Participant recruitment

Patients with severe COVID-19 will be recruited; they will meet the National Diagnostic and Treatment Protocol (the 7th trial version). The participants will be from the Department of Infectious Diseases at Huangshi Hospital of Traditional Chinese Medicine. Recruitment advertisements will be placed on the inpatient, network, WeChat, and Weibo official platforms to enroll potential participants. The informed consent process will be conducted by the principal investigator (LF) or study coordinator (WC) who will screen participants to confirm that potential participants meet the eligibility criteria listed below if the participants agree to sign the informed consent form.

### Inclusion criteria

Patients will only be recruited if they meet each of the following conditions: (1) meet the critical diagnosis criteria for severe COVID-19 [6], (2) are aged between 20 and 80 years and are male or female, (3) have a stable condition and are conscious and cooperative in the examination, (4) volunteer to join the trial and sign the informed consent form, and (5) promise not to perform other exercise programs.

### Exclusion criteria

Those who meet one of the following conditions will be removed: (1) patients with complications of other serious underlying diseases, such as chronic obstructive pulmonary disease, obstructive pulmonary disease, coronary heart disease, and hypertension; (2) patients with serious mental illness; (3) patients with cognitive dysfunction who are unable to understand the trial process and rehabilitation content; (4) patients with severe bone and joint diseases (such as spinal arthritis, severe osteoporosis, and periarthritis) affecting limb function and movement; (4) patients with respiratory failure who require mechanical ventilation or patients with shock or combined organ failure requiring intensive care unit (ICU) monitoring and treatment; (5) pregnant or lactating women; and (6) patients who participate in other forms of exercise during the trial.

### Dropout and suspension criteria

During the intervention period, patients will have the right to withdraw for whatever reason and at whatever time under the protection of the Declaration of Helsinki [16]. In addition, if the hospitalization time is less than 7 days, the subject will be excluded as the outcome evaluation cannot be completed.

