### Interventions

For the emergency event of COVID-19, standard therapy has been developed in strict accordance with the National Diagnostic and Treatment Protocol (the 7th trial version). For patients, standard therapy is necessary to prevent death and other adverse consequences. On the basis of the guideline therapy, the test group will require a standardized TCMR program consisting of acupressure therapy and Liu Zi Jue Qigong exercises. The program will be performed twice a day at 10 am and 4 pm. Each time, acupressure will be performed first, and then Liu Zi Jue Qigong exercises will continue. Each treatment will last 20 min; thus, a total of 40 min will be needed. The TCMR program will be ongoing during the patient’s stay until the patient is discharged. There will be consensus in advance regarding the acupuncture points, pressure levels, and duration. Liu Zi Jue Qigong exercises will be demonstrated live by the therapists on the first day until the patient is able to perform the exercises skillfully. Patients will be provided with paper and video versions of the exercises to facilitate subsequent practice. Therapists performing rehabilitation therapy will be required to have 10 years of clinical experience in acupressure and Qigong therapy and have undergone rigorous clinical trial training before conducting trials until passing an exam to perform the intervention. Furthermore, both groups of the participants will be allowed to participate in normal exercise under the intervention conditions.

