### Primary outcome measurements

#### Modified Medical Research Council (mMRC) Dyspnea Scale

We will use the mMRC as the primary outcome indicator to evaluate the dyspnea symptoms and physical health; this scale is a good indicator of the functional capacity of patients’ lungs [22]. Evaluation of the outcomes will occur at three points (before treatment, the 7th day during hospitalization, and the discharge day). The mMRC [22, 23] grades are as follows: mMRC grade 0, dyspnea occurs only during strenuous exercise; mMRC grade 1—the patient has shortness of breath when walking on flat ground or walking on a small slope; mMRC grade 2—due to shortness of breath, when walking on flat ground, the patient is slower than another person of the same age or needs to stop to rest; mMRC grade 3—when walking on flat ground for approximately 100 m or after a few minutes, the patient needs to stop to pant; and mMRC grade 4—due to severe breathing difficulties, the patient cannot leave the house or has breathing difficulties when dressing or undressing. We will assess the mMRC with a repeated longitudinal analysis.

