### Randomization

Randomization will be performed after the eligibility assessment and baseline assessment. The Department of Science and Technology of SUTCM will generate the randomization sequence using a random number generator (IBM, Chicago, IL, USA) and then placed in a sequenced, sealed, opaque envelope. When potential participants meet the inclusion criteria, the envelope can be opened and the subject will accept the corresponding measures. Then, eligible patients will be randomly divided into a guideline therapy group and a guideline therapy plus TCMR group, with an allocation proportion of 1:1.

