#### Analysis of primary outcome

The primary outcomes will be evaluated at baseline, 6 days after the intervention, and upon discharge based on the intention-to-treat analysis (ITT). The primary endpoint of the trial is the mean change in mMRC Scales from baseline to the discharge day. Baseline covariates included for adjustment were sex, age category, history of cardiopulmonary disease, and body weight category. The whole outcomes scale was also measured at baseline. When the data have a normal distribution, two-way repeated-measures ANOVA will be used as the main analytic method, and a paired sample *t* test will be used between the two intervention groups; if the normal distribution is not met, the Wilcoxon test will be used as an alternative method. Prior to any analysis, any missing data pattern will be investigated and reasons for missing data obtained and summarized where possible. The percentage of missing data is 20%, and we plan to generate 5 imputed datasets, which is the minimum recommended number [28]. The sensitivity analyses were carried out to assess two assumptions about missing data, and data imputation scenarios can potentially influence the primary result [29]. To account for missing data, our primary analyses were conducted on an imputed data set where missing values were generated using multiple imputation by chained equations (MICE) [30].

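### Excluding randomised patients with a hospital stay under 7 days contradicts the intention-to-treat primary analysis, and the stated reason does not hold for a discharge-day endpoint

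*Protocol article*

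**What the plan says.** All places are in the protocol article.

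- **Dropout and suspension criteria:** "if the hospitalization time is less than 7 days, the subject will be excluded as the outcome evaluation cannot be completed". No cause of a short stay (discharge, transfer, death) is treated separately.
- **Randomization:** "Randomization will be performed after the eligibility assessment and baseline assessment".
- **Analysis of primary outcome:** the outcomes are evaluated at baseline, on treatment and "upon discharge based on the intention-to-treat analysis (ITT)". The endpoint is fixed: "The primary endpoint of the trial is the mean change in mMRC Scales from baseline to the discharge day". For incomplete data, "missing values were generated using multiple imputation by chained equations (MICE)".
- **mMRC section:** "Evaluation of the outcomes will occur at three points (before treatment, the 7th day during hospitalization, and the discharge day)".

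A secondary point concerns exercise. Exclusion criterion (6) removes "patients who participate in other forms of exercise during the trial", and inclusion criterion (5) asks for a promise not to follow other exercise programmes. The Interventions section says that "both groups of the participants will be allowed to participate in normal exercise under the intervention conditions".

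**The concern.** An intention-to-treat analysis keeps every randomised patient in the assigned arm. A rule that drops patients because of something that happens after randomisation breaks this, and more so when the event may depend on treatment. Length of stay is such an event. The trial's hypothesis is that adding TCMR improves clinical symptoms, and that could bring discharge forward. Participants and therapists know the allocation, so knowledge of the arm could also influence when a patient leaves.

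A short stay can mean a quick recovery or an early death. If either kind is removed at different rates in the two arms, the arms compared are no longer the arms that were randomised, and adjustment for baseline covariates cannot be relied on to repair this. The rule decides who enters the primary comparison, so the conflict cannot be left open.

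**Working it through.** **1. Timing.** Patients are randomised after the eligibility and baseline assessments. Whether the stay will be under 7 days is unknown then, so the exclusion can only act after randomisation.

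**2. What each patient can provide for the primary endpoint (discharge-day mMRC minus baseline mMRC).**

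| Patient | Baseline | Day 7 | Discharge day | Primary endpoint |
|---|---|---|---|---|
| Discharged on day 10 | yes | yes | yes | observable |
| Discharged on day 5 | yes | no | yes | observable |
| Died on day 5 | yes | no | no | not observable, no rule given |

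The second row shows that the stated reason fails: the rule discards a patient whose primary endpoint can be measured. Only the third row has a real gap, and the article states no way of handling it.

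**3. The plan's sample size.** Inputs from Sample size calculation: means 0.52 and 0.95, SDs 0.11 and 0.92, alpha 0.05 (two-tailed, from General analysis principles), power 0.90, loss 20%.

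- Difference: 0.95 − 0.52 = 0.43.
- Root-mean-square SD: √[(0.11² + 0.92²)/2] = 0.655.
- The unequal-variance t test needs 51 per arm, and 51/0.8 = 63.75, rounded up to 64.

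The stated 64 per group is reproduced, so no figure is wrong here.

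**4. Power, if the exclusions come on top of the 20% loss.** Analysed per arm = 64 × 0.8 × (1 − e), where e is the assumed share excluded.

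| e | Patients per arm | Power |
|---|---|---|
| 0 | 51.2 | 0.90 |
| 10% | 46.1 | 0.87 |
| 20% | 41.0 | 0.83 |
| 30% | 35.8 | 0.77 |

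If the exclusions are already part of the 20%, power stays at 0.90. The article does not say which applies.

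**5. Bias, as an illustration.** The article gives no length of stay, no share under 7 days and no mortality, so the following are assumptions. Improvement and speed of discharge are bivariate normal with correlation ρ, the SD of improvement is 0.655 in both arms, and only early discharges are removed. If the fastest share p is removed, the mean of those kept falls by ρ × 0.655 × φ(z)/(1 − p), where z is the (1 − p) normal quantile.

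- p = 10%: φ(z)/(1 − p) = 0.1755/0.90 = 0.195.
- p = 20%: 0.2800/0.80 = 0.350.
- Shift in the arm difference with 10% of controls and 20% of treated patients removed: ρ × 0.655 × (0.350 − 0.195) = 0.1015ρ.

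| Removed, control / treated | ρ = 0.3 | ρ = 0.5 | ρ = 0.7 |
|---|---|---|---|
| 10% / 10% | 0 | 0 | 0 |
| 10% / 20% | 0.03 (7%) | 0.05 (12%) | 0.07 (17%) |
| 5% / 15% | 0.03 (8%) | 0.05 (13%) | 0.08 (18%) |

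Entries are mMRC points by which the treatment benefit is understated; percentages are shares of 0.43. The zeros require equal shares, equal SDs and equal correlations. With ρ = 0 every entry is zero. Unequal removal of early deaths works the other way, flattering the arm that has more deaths removed, so the sign of the net effect is open.

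**The case against.** **The reason for the rule is not baseless.** The article schedules three assessments and names two-way repeated-measures ANOVA as the main method, and without a day-7 value the three-point series is incomplete. That much stands. It does not justify exclusion, because the primary endpoint uses only baseline and discharge and the article already plans imputation.

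**The rule could be meant for a per-protocol set.** The article names no such set and attaches no population to the rule, so the conflict with intention-to-treat remains.

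Four stronger readings are tempting, and the documents do not support them:

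- *TCMR's best responders are in fact removed.* The rule is the same in both arms, and nothing in the article shows different shares of short stays. Any model of recovery and discharge would need recovery rates and a discharge rule that the article does not give, and would return what was assumed.
- *Early deaths disappear from the trial.* The rule concerns outcome evaluation. Adverse events are still recorded and compared. Patients must be stable at entry, and those needing ventilation or intensive care are excluded, so early deaths may be few. What stands is that the primary analysis has no stated rule for them.
- *Power is lost beyond the 20% allowance.* The rule stands under the dropout heading and may be part of the 20%.
- *The exercise passages flatly contradict each other, and removals would fall mostly on controls.* Ordinary activity as opposed to a competing programme is a natural reading, and the promise in inclusion criterion (5) binds both arms. What stands is unclear wording and a criterion that can only be judged after enrolment.

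**Conclusion.** The point holds. The exclusion of stays under 7 days and the intention-to-treat primary analysis cannot both be followed, and the reason given for the exclusion does not apply to a change from baseline to discharge day. This conclusion rests on the protocol's text alone and needs no assumption about the data.

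That the rule biases the result is a risk, not an established fact. It arises if treatment or unblinded care changes length of stay or survival. Under the illustrative assumptions the understatement is 0.03 to 0.08 points on a planned difference of 0.43 when exclusion differs by 10 percentage points, and nil when exclusion is equal. Those figures use a common SD of 0.655, although the plan's own SDs are very unequal (0.11 and 0.92), and they leave out deaths. Neither direction nor size can be determined from the documents. The exercise wording is a minor, separate matter.

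**What to change.** 1. Delete the under-7-day exclusion from Dropout and suspension criteria.
2. State that all randomised patients are analysed as randomised. For those discharged before day 7, use the discharge-day mMRC for the primary endpoint and treat the day-7 value as missing under the planned MICE.
3. State how deaths before discharge enter the primary analysis.
4. Confine any population with stays of 7 days or more to a sensitivity analysis, and report the number of shorter stays by arm with the cause.
5. State whether the 20% loss allowance was meant to cover short stays.
6. Reconcile inclusion criterion (5) and exclusion criterion (6) with the Interventions section on exercise. Keep patients who take other exercise after randomisation in the intention-to-treat set and record this as a protocol deviation in both arms.

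The cost is protocol wording. The sample size stays at 64 per group, the discharge assessment is already scheduled and imputation is already planned. Protocol version 3 (8 July 2020) is dated after the expected end of recruitment (30 June 2020), so the change should be documented before the data are locked, while the statisticians are still blinded. If patients have already been excluded under the rule, their discharge assessments should be retrieved where they were made, and otherwise counted as missing.
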